### Quality control

2.7

Main researchers in this trial will be asked for Good Clinical Practice certificates and the other researchers will receive relevant training on the qualifications required for clinical trials to ensure the quality of the research. All researchers will perform operations in accordance with Standard Operating Procedures to make sure the consistency of the research. The test results will be saved in the original documents, laboratory results and records. The original data will be registered in the electronic case report form (e-CRF) and the data uploaded in the e-CRF is parallel to the original data. Kernel researchers will verify the accuracy of the original data. The data will be analyzed independently by different statisticians. The data may be used to do interim analyses, and the monitor will supervise the whole study period and make the final decision if terminate the trial.

All participants will be collected blood samples and stool samples at the research hospital site when participating in the study for the first time. The laboratory will assist in the collection of samples, and the main researchers will collect and evaluate the samples. Longhua Hospital, Shanghai University of Traditional Chinese Medicine will provide sample processing, aliquoting and storage facilities. All samples will be placed in the storage warehouse of the hospital after centrifugal extraction, and stored in a liquid nitrogen refrigerator at -80°C. All samples will be coded with a unique number. Any process involving sample transfer will strictly abide by the sample transfer operating specifications. These processes will be supervised by the Medical Ethics Committee of Longhua Hospital.

### Informed consent and data confidentiality agreement

2.8

The investigator is responsible for explaining the purpose, methods, benefits and potential risks of this trial to each participant and obtaining informed consent signed by the participants. For participants who are unable to sign the informed consent form by themselves for any reason, it must be signed by their legal representative instead. In addition, in the informed consent form, we attached a clause: consent to allow clinical investigators, research supervisors, ethics committees, and drug regulatory authorities to check the original clinical research data, in order to verify the reliability of the data results. This clause will also obtain the informed consent of the participants.

The investigator must follow the principle of confidentiality when recording the trial data of the participants. When uploading participants’ information into the e-CRF form, 2 researchers will input data independently, and conceal personal information such as the participant's name and address, and protect the participant's personal information before, during, and after the trial. Participants’ medical records (research medical records, physical and laboratory examination reports, etc.) will be kept in the hospital intact, and doctors will record the results of laboratory examination in the participants’ outpatient medical records. Any public report on the results of this trial will not disclose the personal identities of participants. We will make every effort to protect the privacy of participants’ personal information within the scope permitted by law.

Sample information will be electronically transmitted to the Statistics Center for verification and it will be kept strictly confidential. The information provided to researchers will not contain personal identification of participants. Researchers have no access to personal identifiers, nor will they be able to link these test results with personal identifier information. No individual results will be shown in publications or other reports. There are related regulations in the informed consent form. When the participants sign the consent form, they agree to collect and submit additional blood samples and stool samples for storage and future testing. Participants will check it out as an additional item.

### Trial status

2.9

The trial started in May, 2020 and is currently recruiting. The planned end of the study is at the end of May, 2021.

## Discussion

3

This study protocol is for a single-arm, non-randomized, open, exploratory clinical trial which aims to evaluate the efficacy and safety of DN-powder in intervention of MS and to explore the mechanism of action through multi-group correlation analysis.

For now, early diagnosis and lifestyle changes are still the first choice to intervene MS. Lifestyle interventions include control, proper exercise, changes in eating habits, smoking cessation and moderate drinking. For those who have taken preventive measures but failed to reduce risk of disease, corresponding medications should be taken for each component.^[21]^ Traditional Chinese Medicine (TCM) has few side effects, high clinical safety, low price and easy access which expands the boundaries of modern medicine.

Recent years, a large number of experimental studies have shown that DN plays an important role in glucose and lipid metabolism. Some studies have shown that DN can reduce the serum levels of alanine aminotransferase and aspartate aminotransferase, make attenuation of malondialdehyde production, and improve ultrastructural morphology in hepatocytes to reduce the liver damage relevant to CCl4. DN is also beneficial to the gene expression of glucose and lipid metabolism which can enhance the expression of genes related to the Nrf2-antioxidant pathway.^[22,23]^ In addition, DN possess anti-oxidative effects, and its total alkaloids can prevent LPS-induced neuroinflammation.^[24]^

This clinical trial will provide information on the efficacy and safety of taking DN- powder orally in the intervention of MS. Not only in terms of physical measurements, but also about biomedical variables. The trial will be conducted on the basis of evidence-based medicine and provide conclusive evidence.

The trial takes a rigorous design that meets clinical requirements. As far as we know, this is the first exploratory trial of taking DN- powder orally in the intervention of MS. The result will be used to verify and carry out other clinical studies on the intervention of TCM in MS.

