### Trial design and study setting

2.1

The trial is designed as a single-arm, non-randomized, open, exploratory clinical one. The protocol was written in accordance with Standard Protocol Items: Recommendations for Interventional Trials 2013 statement.^[15]^ The study protocol was approved by The Medical Ethics Committee of Longhua Hospital, Shanghai University of Traditional Chinese Medicine (No: 2020LCSY021), and informed consent will be obtained from each participant.

The trial will be conducted in Longhua Hospital, Shanghai University of Traditional Chinese Medicine, from July 2020 to June 2021 and 30 qualified participants will be recruited from public and will be allocated to the therapy group for 2 months. The flowchart is shown in Figure 1, and the timeline is given in Table 1.

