#### Inclusion criteria

2.2.1

Participants who meet all the following criteria will be recruited:

1.Aged between 18 to 65 years old, both genders;2.Meet the diagnostic criteria of MS:^[16–18]^① Overweight or Central obesity: BMI cut-off point for obesity (>24.0 kg/m^2^) or waist circumference ≥90 cm for males and ≥85 cm for females.② Hyperglycemia: fasting plasma glucose (FPG) ≥6.1 mmol/L (110 mg/dl) or 2 hour plasma glucose ≥7.8 mmol/L (140 mg/dl), or previously diagnosed type 2 diabetes.③ Hypertensive: systolic blood pressure ≥130 or diastolic blood pressure ≥ 85 mm Hg, or treatment of previously diagnosed hypertension.④ Raised TG level: fasting TG level≥1.7 mmol/L (150 mg/dl), or received treatment for this lipid abnormality.⑤ Reduced HDL-c: fasting blood HDL-c<0.9 mmol/L (35 mg/dl) for males and <1.0 mmol/L (39 mg/dl) for females.^∗^with 3 or all of the above 5 items can be diagnosed as metabolic syndrome.3.Agree to join this clinical study, volunteer to sign up informed consent form and agree to participate in all visits and inspections in accordance with the requirements of the study protocol.

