##### Diet intervention

2.3.3.1

Helping participants to establish a healthy diet refer to *Dietary Guidelines For Americans 2015–2020*^[19]^ which including focusing on diversity, nutritional density and quantity of foods; limiting the energy supply of sugars and saturated fatty acids; reducing sodium intake; switching to choose healthy foods and beverages. The total calories intake per day should be 2000 for female and 2400 for male.

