##### Exercise prescription

2.3.3.2

The exercise prescription follows FITT principle which stands for frequency, intensity, time, and type of exercise. According to American College of Sports Medicine guidelines for exercise testing and prescription^[20]^ and requiring participants to do 150 minutes of moderate-intensity aerobic exercise (50%–70% of maximum heart rate; maximum heart rate = 220 - age) every week and record it.

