#### Combination medication statement

2.3.6

After joining the group, participants must maintain a standardized diet and a relatively stable amount of exercise. During the study period, no therapeutic drugs other than those specified in the study should be used; those with other diseases that must taking other drugs should be recorded in detail by the researcher.

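### The Discussion promises conclusive evidence on DN-powder, but a single-arm before-after study of DN-powder given together with diet and exercise cannot isolate its effect.

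*Protocol article*

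**What the plan says.** **Claim.** Section 3 (Discussion) says that the study "aims to evaluate the efficacy and safety of DN-powder in intervention of MS" and then: "The trial will be conducted on the basis of evidence-based medicine and provide conclusive evidence".

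**Design.** Section 2.1: "The trial is designed as a single-arm, non-randomized, open, exploratory clinical one". Section 2.5 sets n = 30 by expert consultation, without a calculation. Section 2.6 judges efficacy by comparing outcomes before and after the intervention, with P < .05 for each outcome.

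**What participants receive.** Besides DN-powder (section 2.3.2), everyone gets two further interventions:
- Diet (section 2.3.3.1): "Helping participants to establish a healthy diet", with a daily calorie figure for each sex and "limiting the energy supply of sugars and saturated fatty acids".
- Exercise (section 2.3.3.2): "requiring participants to do 150 minutes of moderate-intensity aerobic exercise" every week, with a record kept.

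Section 2.3.6 adds that, once enrolled, "participants must maintain a standardized diet and a relatively stable amount of exercise". No comparison group and no period on diet and exercise alone are described. The Discussion itself places lifestyle change, with early diagnosis, ahead of medication for this condition.

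**Outcomes and entry.** The primary outcomes (section 2.4) are TG, total cholesterol, HDL-c, LDL-c, free fatty acid and FPG; weight and BMI are also followed. TG, FPG and HDL-c appear again among the five diagnostic items in section 2.2.1, of which three are needed. The TG item, for example, reads "fasting TG level≥1.7 mmol/L (150 mg/dl), or received treatment for this lipid abnormality". Table 1 puts the eligibility check and the first laboratory values in the same time-0 column.

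**The concern.** The question posed is what DN-powder does. The data can only answer what happens over 8 weeks to people given DN-powder, a diet and an exercise prescription together. Lipids, glucose, weight and BMI are what diet and exercise are meant to move, so any improvement has at least two candidate causes that always occur together. No analysis of these data can separate them.

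The safety half of the claim has a similar limit: with 30 people, a clean record leaves a fairly wide range of event rates possible.

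At stake is the headline conclusion. The abstract says that the results may support DN-powder as an alternative therapy for some patients, and its methods mention DN-powder but neither the diet nor the exercise. A significant before-after change, read against the promise of conclusive evidence, would be taken as proof for the powder.

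**Working it through.** The plan gives no effect size, SD or power behind n = 30, so it has no figure to reproduce. The calculations below show how far a before-after P value can mislead. All shift sizes and SDs are assumptions.

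**1. Inert powder, change from other causes.**
Inputs: n = 30 (section 2.5); P < .05 per outcome (section 2.6), taken as two-sided. A paired t test with complete data stands in for the before-after comparison. Assumed mean change from causes other than DN-powder: d SD of the change.
The statistic follows a non-central t with 29 degrees of freedom and non-centrality d√30. The critical value is 2.045.

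| d | d√30 | P(significant) |
|---|---|---|
| 0.1 | 0.548 | about 8% |
| 0.2 | 1.095 | about 19% |
| 0.3 | 1.643 | about 36% |
| 0.4 | 2.191 | about 56% |
| 0.5 | 2.739 | about 75% |

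The test reaches 80% power at d = 0.53 whatever the cause of the change.

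**2. Regression to the mean, TG as the example.**
This applies only if the time-0 sample also decided eligibility. Assumed on the log scale: within-person SD w = 0.20 to 0.25, between-person SD b = 0.40 to 0.45, population geometric mean G = 1.5 to 2.0 mmol/L, and everyone selected on TG ≥ 1.7 mmol/L.
With s = √(w² + b²) and a = (ln 1.7 − ln G)/s, the expected untreated log change is −(w²/s) × φ(a)/(1 − Φ(a)).
- Smallest: w = 0.20, b = 0.45, G = 2.0. Then s = 0.492, a = −0.330, ratio = 0.600, and the change is −(0.0400/0.492) × 0.600 = −0.049, a fall of about 5%.
- Largest: w = 0.25, b = 0.40, G = 1.5. Then s = 0.472, a = 0.265, ratio = 0.974, and the change is −(0.0625/0.472) × 0.974 = −0.129, a fall of about 12%.

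Simulated trials of 30 over the same settings give P < .05 in about 16% to 53%.

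The figure is lower when only some participants qualify through the marker. In a separate simulation, half were selected on a value more than 0.5 SD beyond the mean and the rest were unselected. It gave significant improvement in 28% of trials at an assumed baseline-to-week-8 correlation of 0.6, and in 10% at 0.9.

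**3. Safety.**
With zero events in 30, the upper limit is 1 − 0.05^(1/30) = 9.5% (one-sided 95%) or 1 − 0.025^(1/30) = 11.6% (two-sided 95%).

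**The case against.** The strongest reply is that the design is openly labelled exploratory, that exploratory trials need no control arm, that the abstract is hedged, and that the Discussion looks ahead to further studies. Most of that stands. A single-arm exploratory trial is legitimate, and the design is not the fault here. The reply does not rescue the sentence that promises conclusive evidence, which claims a property the design does not have.

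The lifestyle shift is also assumed. At 0.1 to 0.2 SD, the chance of a significant result with an inert powder is only about 8% to 19%. That is fair and is why the whole range is shown. The attribution problem does not depend on where in the range the truth lies.

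A reader might infer more than the documents support:
- **That baseline and eligibility use the same blood sample.** Table 1 has one time-0 column, but it does not say that the values come from one sample. This is an inference from a condensed table.
- **That all outcomes drift back to the mean.** Total cholesterol, LDL-c and free fatty acid are not entry criteria. For TG, FPG and HDL-c, only participants who qualified on a measured value are affected. Section 2.2.1 also admits people through obesity, blood pressure, 2-hour glucose, known diabetes or treated lipid abnormality.
- **That sections 2.3.6 and 2.3.3.2 contradict each other on exercise.** They do not: a fixed weekly amount can be a stable amount.
- **That the programme is new to every participant.** The wording on establishing a diet and the absence of a run-in suggest it, but prior habits are not stated.

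**Conclusion.** The point holds as a mismatch between claim and design. The trial can estimate the before-after change under DN-powder combined with diet and exercise. It cannot attribute that change to DN-powder, and 30 people cannot settle safety.

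The confounding follows from the protocol's text alone, covers all six laboratory outcomes plus weight and BMI, and is enough by itself. The false-positive probabilities rest on assumed shifts and show direction and range only. Regression to the mean is a conditional addition: it is limited to three outcomes and depends on the inferred shared time-0 sample. None of this shows that DN-powder is ineffective or that the single-arm design must be abandoned.

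**What to change.** Replace the promise of conclusive evidence in the Discussion with:

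> The trial estimates the before-after change under DN-powder combined with diet and exercise; it cannot separate the effect of DN-powder and will inform a controlled trial.

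Align the abstract and the stated aim with this, and interpret any before-after P < .05 in the same terms. Change by recorded weekly exercise minutes may be shown, but descriptively only: it compares self-selected adherence in at most 30 people and does not isolate the powder.

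Two additions that may suggest themselves are not recommended:
- **A second baseline sample for those still to be enrolled.** Recruitment is under way (section 2.9), so this would leave two baseline definitions within 30 people, add a procedure and shift the start of treatment.
- **Analysing those who did not qualify through the marker as a check on regression to the mean.** They are selected low. Under the TG assumptions above, their expected untreated drift is upward by about 5% to 15%, so one bias replaces another.

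The cost is a few sentences, with no new data or procedures. The stated claim becomes less favourable.
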